##### The primary data set

Clinical tests and scores:

The following clinical tests were chosen to describe the subject’s clinical condition as precisely as possible. The tests include measures for the impairment of UE function, which is the main focus of the study, but also other stroke symptoms, such as aphasia and neglect and other conditions (e.g., depression) that might affect the rehabilitation process. In the following section each test is described in detail:

National Institutes of Health Stroke Scale (NIHSS): The NIHSS is part of the usual highly standardized stroke workup. It consists of 15 items that can be scored with 0 to a maximum of 2–4 points. The score ranges between 0 and 42 points, with 0 indicating no deficit and 42 the maximum possible deficit. It is used to measure stroke severity and suitable to detect improvement or deterioration of the patient. The NIHSS has a high reliability (κ = 0.77) and validity (high correlation with CT lesion and clinical outcome, with Spearman’s correlations of 0.74 and 0.71, respectively) [13].

FM-UE and sensation: The FM-UE and sensation describes the sensorimotor impairment of the arm after stroke. It consists of 33 items for motor function scored from 0 to 2. A high score corresponds to high function. Reliability and validity is high, especially for motor function [26, 31]. The FM-UE is not part of the usual stroke workup. The change of the FM-UE after 90 days compared to the initial score obtained on the stroke unit during the acute phase after stroke related to the initial FM-UE impairment (for specific definition, see “Outcome”) will serve as the primary endpoint of this study. In addition, the FM-UE for sensation (6 items with scores 0–2) will be additionally assessed, but only for the primary data set. It will not serve as an endpoint of this study.

Shoulder Abduction Finger Extension (SAFE) score: To calculate the SAFE score, shoulder abduction and finger extension strength are measured using the classification of the British Medical Research Council (MRC). The MRC scale scores muscle strength from 0 (no movement) to 5 (normal power) [32]. Accordingly, the SAFE score ranges from 0 to 10. A score of 5 or more predicts a good or excellent outcome after stroke affecting the UE [4]. It is not part of the usual stroke workup.

Grip strength: The grip strength can be quantified using a dynamometer and is given in kilogram. The best out of three trials will be evaluated. It is not part of the usual stroke workup.

Bells test [33]: The Bells test assesses neglect by requesting the subjects to cross all the bells (*n* = 35) mixed with distractors (*n* = 280) on a sheet of paper. Missing out 5 bells ore more counts as evidence for neglect [34]. The Bells test shows a low learning effect and, therefore, can be used for repeated testing. It is not part of the usual stroke workup.

Aphasia Quick Test (German: Aphasie-Schnelltest) (AST): The AST is a short test for patients with acute aphasia inspecting comprehension, talking, reading and writing. It is scored from 0 to 31, a low score reflects severe aphasia. Validity and reliability is moderate to good (Kendall correlation coefficient 0.75–0.82 and Spearman’s correlation 0.68–0.82, respectively) [22, 35]. It is not part of the usual stroke workup.

mRS: The mRS is a widely used test to determine impairment and dependency after stroke on a scale ranging from 0 (no symptoms) over 1 (symptoms but no disability), 2 (slight disability), 3 (requires help, but can walk without assistance), 4 (cannot walk without assistance), 5 (bedridden, severe disability, requires constant nursing) to 6 (death). Reliability is moderate to good. Validity measured by correlation with infarct volume is moderate. This is comparable to other scales like the BI [6]. It is part of the usual stroke workup.

BI: The BI measures performance in activities daily life. Ten items can be scored from 0 to 5–15 points maximum, adding up from 0 to 100 points. A high score reflects high independence. Reliability is high [27], validity is moderate (measured by correlation with infarct volume) [6]. The BI is part of the usual stroke workup.

ARAT: The ARAT assesses motor activity performance of the UE after stroke. It consists of the subscales grasp, grip, pinch and gross movements which are scored from 0 (no movement) over 1 (movement only partially possible), 2 (movement possible but only with great difficulty or much time is needed) to 3 (normal movement), adding up to 57 points maximum. A score less than 10 points reflects severe impairment. Reliability is high (Cronbach’s alpha 0.97), and validity is moderate to good (ρ = 0.45–0.76) [36]. It is not part of the usual stroke workup.

SS-QOL scale: The SS-QOL scale measures health related quality of life. It consists of 49 items that are scored from 1 to 5, adding up to 49–245 points. A high score reflects high quality of life. Reliability is high (Cronbach’s alpha 0.73–0.89) with excellent content validity [24]. It is not part of the usual stroke workup.

Beck’s Depression Inventory (BDI): The BDI is a depression screening tool consisting of 21 items that are scored from 0 to 3, adding up to 0 to 63 points. A high score reflects high probability of depression, the threshold for the diagnosis of depression is 10. The BDI is reliable, content and convergent validity in particular is high, while differentiating from anxiety is poor [37]. It is not part of the usual stroke workup.

Diagnostic Instrument for Limb Apraxia (short version) (DILA-S): The DILA-S consists of 6 subscales: I. Imitation of meaningless gestures, II. Familiar Tool Test, III. Pantomime the usage of tools, IV. Imitation of meaningful gestures, V. Novel Tools and VI. Naturalistic Action Test – Breakfast Task [38]. We will only use subscale I and III.

I. Imitation of meaningless gestures: This subscale consists of 10 items. Each item is demonstrated by the examiner and has to be repeated by the subject with the non-impaired limb. The items are scored from 2 (correct imitation at the first try) over 1 (correct imitation at the second try) to 0 (false imitation). Consequently, a low score reflects severe apraxia. Interrater-reliability is high (97% congruence) and validity sufficient (r ≥ 3.39, *p* ≤ 0.003) [38]. It is not part of the usual stroke workup.

III. Pantomime the usage of tools: This subscale contains 8 items. Every item is a tool, for instance a key, that is presented on a picture and explained to the patient by the examiner. After demonstration the subject is asked to mimic the usage of the tool (e. g., open the door with a key) using the non-impaired limb. Each item is scored from 2 (correct at the first try), over 1 (correct at the second try) to 0 (total error). Hence, a low score corresponds to severe apraxia. Interrater-reliability is high (95% congruence) and validity sufficient (r ≥ 3.39, *p* ≤ 0.003) [37]. It is not part of the usual stroke workup.

In addition to these clinical tests and scores, other relevant clinical data (e. g., vital parameters, medication) will be collected. In the University Hospital of Tübingen these data will be retrieved semi-automatically from the primary clinical data information systems, while it will be inserted manually at the collaborating acute-care hospitals.

Laboratory workup:

Routine laboratory workup as part of the usual stroke workup will be collected with attention to sodium, calcium, CRP, d-dimers, NT-proBNP, troponin, international normalized ratio (INR) and activated partial thromboplastin time (aPTT). The selection of parameters is based on demonstrated correlations with stroke outcome [14–17, 39].

Neuroimaging:

For each participant structural neuroimaging will be acquired. Structural magnetic resonance imaging (MRI) comprises diffusion weighted imaging (DWI), fluid attenuated inversion recovery (FLAIR) and magnetic prepared-rapid gradient echo (MP-RAGE) sequences. Structural MRI data will be acquired at a 1.5 or 3 Tesla MRI scanner. Before scanning, patients are evaluated by a medical doctor for MRI contraindications. If MRI is not available or contraindicated, a cranial computed tomography (CT) will be performed. MRI/CT is part of the usual stroke work-up. There will be no additional study-related scanning beyond the clinical standard.

The images will be used to calculate lesion volume, and check for involvement of the pyramidal tract and other strategic locations influencing motor outcome [7]. The strategic locations are the primary motor cortex (M1), the corona radiata (with or without affecting the pyramidal tract), internal capsule (with or without affecting the pyramidal tract), corpus callosum, lentiform nucleus (putamen and globus pallidus), caudate nucleus, thalamus, crus cerebri (with or without affecting the pyramidal tract), mesencephalon (with or without affecting the pyramidal tract), pons (with or without affecting the pyramidal tract), medulla oblongata (with or without affecting the pyramidal tract), upper, middle or lower cerebellar peduncle.

Electrophysiological data:

EEG: At the University Hospital of Tübingen resting-state EEG will be obtained using a 21-channel (in patients with severe stroke) or 64-channel (in patients with non-severe stroke, who tolerate a longer procedure) gel filled sintered ring electrode EEG cap (EasyCap, Munich, Germany) and an optically isolated battery powered biosignal amplifier (Brain Products, Gilching, Germany). EEG will be recorded with eyes closed and eyes open for 3 min each. The other acute-care study centers will use a 21-channel EEG (TrueScan (DEYMED Diagnostic GmbH, Weimar, Germany), Natus Brain Monitor (Natus Europe GmbH, Planegg, Germany), EEG-40 T or EEG-29 T (Monitor (Natus Europe GmbH, Planegg, Germany), respectively).

The resting-state EEG will be analyzed using the pairwise devised Brain Symmetry Index (pdBSI) and the (delta+theta)/(alpha+beta) power ratio (DTABR). The BSI (or pdBSI if the data is assessed from homologue channels from both hemispheres) describes the ipsilesional/contralesional power (a)symmetry by quantifying the difference in mean spectral power per hemisphere across 1–25 Hz [11, 12]. As the term DTABR already implicates, slow (delta and theta) and fast (alpha and beta) brain oscillations are put in relation to each other. The DTABR and the pdBSI predict impairment as rated by the modified Rankin Scale (mRS) 6 months after the stroke event [11, 12].

Motor evoked potentials: MEPs are elicited by TMS and recorded by surface EMG. TMS is a technique that evokes action potentials in the cortex with a spatiotemporal precision of millimeters and milliseconds. In the primary study center a conventional TMS stimulator (MagPro Compact, MagVenture GmbH, Willich, Germany) and stimulation coil (C-B60, MagVenture GmbH, Willich, Germany) will be used. Surface EMG will be obtained through an optically isolated battery powered biosignal amplifier (Brain Products, Gilching, Germany) using bipolar electrodes from arm and hand muscles (extensor carpi radialis (ECR) and first dorsal interosseous (FDI) muscle) on the paretic and non-affected sides. In the collaborating study centers the DuoMAG MP (DEYMED Diagnostic GmbH, Weimar, Germany) and Magstim 200^2^ (ANT Neuro, Netherlands) magnetic stimulators will be used.

MEPs are measured with pre-innervation of the target muscle or, if not possible, the contralateral homologue muscle and maximum stimulator output (if required) to determine if the patient is MEP- or MEP+. The outcome MEP+ requires at least 50 μV peak-to-peak amplitude MEPs in the target muscle in at least 5 out of 10 consecutive trials. MEPs are one of the most researched and robust biomarkers in stroke outcome prediction. Positive predictive value (PPV) (if the patient is MEP+) is 1.0, while the negative predictive value (NPV) (if the patient is MEP-) is 0.74 [18].

##### The neurorehabilitation data set

In the rehabilitation facilities number and duration of therapies will be documented and classified according to the type of neurorehabilitative training. The rehabilitative treatments will be reported using the remedy position number. This is a number allocated to each rehabilitative treatment to make them transparent to the cost centers, i.e., the health care or pension insurance. To ensure that these interventions do not differ between the participating rehabilitation hospitals, they will be checked for complete congruence across hospitals.

In addition, therapy-influencing co-factors, namely support by relatives, motivation, additional self-training and relationship between patient and therapist are registered using a questionnaire with a Likert scale from 0 to 3 (never/very poor to daily/very good). This questionnaire is filled in by the primary therapist (usually a physiotherapist or an occupational therapist). Furthermore, intercurrent diseases during the stay in the rehabilitation facility possibly compromising the rehabilitation process will be registered.

In addition to the rehabilitation training, the FM-UE, the mRS and the BI will be documented on admission, in intervals of 14 days and on discharge.

### Plans to promote participant retention and complete follow-up

The data will be collected on the stroke units of the collaborating acute-care hospitals (primary data set) and the rehabilitation hospitals (neurorehabilitation data set) in a clinical setting defined by current guidelines for stroke care and neurorehabilitation. It is, therefore, not expected that patients discontinue their participation in this study. Only the final examination 90 days after the stroke event will be performed, in most cases, outside of clinical treatment. It will take place in the University Hospital of Tübingen or in the rehabilitation hospital, if the participant is still in rehabilitative treatment. If a participant is unable to come to the University Hospital of Tübingen for the final examination, he will be visited at home by members of the study team.

### Data management

All data of this study will be centrally stored in a clinical data capture system (REDCap®) [39, 40] operated in a secure environment by the Medical Data Integration Centre (meDIC) of the University Hospital Tübingen. Data will be inserted manually or transferred automatically from primary clinical information systems as available, and finally manually curated in the REDCap® data bank. Data from the rehabilitation hospitals and the collaborating acute-care study sites will be entered via web-interface of the secure databank. For each value a range is defined, triggering a warning, if the value lies outside the range. A warning also occurs in case data is missing. Volume cloning ensures instantaneous data backup. Pseudonymized data will be stored for a minimum of 10 years to enable data reanalysis and sustained availability.

### Confidentiality

Data acquisition and storage is performed in accordance with the regulatory requirements of General Data Protection Regulation (GDPR) directives. Case report forms or other data that might be photocopied for verification by authorized persons will be pseudonymized, i.e., they will not contain the name of the participants but only their unique identification code. The identification code consists of an abbreviation plus the number of the participant. Published data (e.g., in form of a scientific oral presentations or publications) will only contain sufficiently anonymized data. Participants’ files will be saved using codes in order to protect their privacy.

Plans for collection, laboratory evaluation and storage of biological specimens for genetic or molecular analysis in this trial/future use.

A blood sample of each participant will be collected and stored in the local biobank (Hertie Institute for Clinical Brain Research) to provide a resource for possible further studies to determine fluid biomarkers for stroke outcome. This will be done only in those participants agreeing to an additional broad informed consent for storage and future testing (including possible genetic analyses). The scientists carrying out analyses on these materials will not have access to personal identifiers and will not be able to link the results of these tests to personal identifier information. No individual results will be presented in publications or other reports. Participants will not be informed on an individual basis of any results from these studies.

### Statistical methods

Statistical methods for primary and secondary outcomes.

Only those participants will a complete data set (including the 90 days follow-up examination or a lethal outcome) will be included in the statistical data analysis. Previous studies suggested that the FM-UE endpoints (i.e., the change in FM-UE 90 days after the stroke event compared to the initial FM-UE, see definition under “Outcome”) or the recovery trajectories of FM-UE scores can be clustered into 3 to 5 subgroups [4, 40]. We will first use time series clustering methods such as mixture of Gaussian processes [41] to identify such subgroups, then use the inferred cluster labels to build a classifier using lasso-regularized logistic regression to predict the group membership of the patient as a function of the primary data set and rehabilitation data set detailed in Tables 2, 3. The lasso regularization can automatically select a sparse subset of the significant features, reducing the dimensionality of the feature space and potentially the sample size required. We will use a nested-cross validation setup to tune the regularization strength via the 1SE-rule [29]. We can then use the Gaussian process model of the respective group to predict the primary endpoint and obtain estimates of the fraction of the explained variance of the total variance in the primary end point on data not seen during model training. If the linear model proves insufficient or unsatisfying, we will resort to non-linear regression models such as Generalized Additive Models (GAMs), which allow flexible nonlinear transformations of individual features of pairs of features [42]. Models for secondary endpoints will be built as well.

Interim analyses are not planned since this an observational study without interventions. No further analyses are planned apart from what is described under statistical methods for primary and secondary endpoints. Biobanking of blood samples will allow future (not yet planned) analyses of the relation of blood markers to stroke rehabilitation outcome.

Methods in analysis to handle protocol non-adherence and any statistical methods to handle missing data.

Before model development with participant data will be started, algorithms will be tested with artificial data sets including sets with missing data. Effective algorithms such as nearest neighbors imputation [43] or multivariate imputation [44] on simulated data-sets with missing data will be used as candidate-algorithms for analysis of the empirical data.

Plans to give access to the full protocol, participant level-data and statistical code.

The study protocol is already accessible to the public on the website of the primary study center (https://hih-tuebingen.de/en/research/neurology-and-stroke/research-groups-and-foci/brain-networks-and-plasticity/) [45]. The statistical code will be available in GitHub. Participant-level data can be provided anonymously.

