**Methods:**

The study is designed as a multi-centre prospective clinical observational trial. An extensive primary data set of clinical, neuroimaging, electrophysiological, and laboratory data will be collected within 96 h of stroke onset from patients with relevant upper extremity deficit, as indexed by a Fugl-Meyer-Upper Extremity (FM-UE) score ≤ 50. At least 200 patients will be recruited. Clinical scores will include the FM-UE score (range 0–66, unimpaired function is indicated by a score of 66), Action Research Arm Test, modified Rankin Scale, Barthel Index and Stroke-Specific Quality of Life Scale. Follow-up clinical scores and applied types and amount of rehabilitation treatment will be documented in the rehabilitation hospitals. Final follow-up clinical scoring will be performed 90 days after the stroke event. The primary endpoint is the change in FM-UE defined as 90 days FM-UE minus initial FM-UE, divided by initial FM-UE impairment. Changes in the other clinical scores serve as secondary endpoints. Machine learning methods will be employed to analyze the data and predict primary and secondary endpoints based on the primary data set and the different rehabilitation treatments.

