### Recruitment

All acute stroke patients (> 2000 per year in the University Hospital of Tübingen and the 4 cooperating acute-care hospitals of the Center of Neurovascular Diseases) will be screened for recruitment, which is planned for a duration of 1.5 years. Up to 70% of all stroke patients present with UE paresis [2, 30], thus about 2000 patients (2000 patients /year × 1.5 years (recruitment period) × 0,7 (percentage of patients presenting with affection of UE)) are available for recruitment in theory. In practice (according to a preparatory analysis of our stroke unit data base over the preceding 2 years), approximately 60% of these patients will not have a sufficient deficit defined as FM-UE ≤ 50 initially or they will have a sufficient deficit, but it will not lasting beyond 96 h resulting in the patient not being in need of rehabilitation of the UE and not eligible for the project anymore (since he or she is not meeting the inclusion criteria anymore), or will die or be too frail for rehabilitation treatment, or will not fulfil the inclusion/exclusion criteria to begin with. Out of the remaining group of 800 patients there will be an expected further attrition by approximately 50% due to unwillingness to participate in the study or failure to obtain written informed consent, leaving approximately 400 patients for recruitment (i.e., a safety margin of 100 patients given the planned inclusion of 300 patients).

Unfortunately, the recruitment process showed that despite the conservative calculation we will probably only reach 200 patients.

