## Discussion

The primary objective of the present study is to identify markers in the acute phase of stroke predicting recovery of UE motor function and determine the most suitable neurorehabilitative treatment in a given patient based on the acquired data sets using machine learning algorithms.

Although we aim to include the whole spectrum of stroke patients (with a FM-UE ≤ 50 points, indicating a relevant deficit), it is possible that the majority of recruited patients will have relatively mild impairment as the whole test battery and the additional electrophysiological examinations might be viewed as strenuous, particularly for severely affected patients. Thus, the data set might be biased towards less affected patients. However, some of the clinical tests and the neuroimaging are part of the usual stroke work-up anyways, and the additional clinical and electrophysiological tests are designed to be executed with a minimal amount of active participation. Thus, we assume that we will be able to collect sufficient data of severely affected stroke patients, in order to draw generalizable conclusions from the study findings.

Whereas the collection of the primary data set in the stroke units is relatively straightforward, it might be more difficult to encompass the rehabilitation process, which is heavily influenced by motivation of the patient and support by relatives. Therefore, we invested a lot of effort in creating items for documenting these aspects of the rehabilitation process by a questionnaire capturing these potentially influencing factors. Hence, we assume we will be able to gather a comprehensive data set of the rehabilitation process.

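### The rule that only participants with a complete data set are analysed conflicts with the plan to impute missing data, so the analysis set is not defined

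*Protocol article*

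**What the plan says.** Two statements in the Statistical methods section of the protocol article bear on who is analysed.

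- The opening sentence sets the analysis population: "Only those participants will a complete data set (including the 90 days follow-up examination or a lethal outcome) will be included" in the analysis.
- The paragraph on non-adherence and missing data says that algorithms will first be tried on artificial data, some of it with gaps, and that "nearest neighbors imputation [43] or multivariate imputation [44] on simulated data-sets with missing data will be used as candidate-algorithms for analysis of the empirical data".

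The article does not define a complete data set. The same section names the predictors as the primary and rehabilitation data sets of Tables 2 and 3. The Participant timeline makes the clinical tests, and at 49–96 h also EEG and MEP, depend on what the patient can manage. The Eligibility criteria admit patients who cannot consent themselves, through a legal representative.

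**The concern.** The two statements answer the same question differently. One removes incomplete records; the other fills them in. An analyst following the article cannot tell whether a patient with a day-90 FM-UE but no aphasia test or EEG belongs in the primary analysis.

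The choice affects both the number and the type of patients analysed. The battery is long and includes tasks that an aphasic, drowsy or severely impaired patient may not finish: a cancellation test, an aphasia test, a 21-item depression inventory and a 49-item quality-of-life scale. A strict rule would tend to drop such patients after they were enrolled. The Discussion already concedes that recruitment may favour milder cases because the battery "might be viewed as strenuous, particularly for severely affected patients". A complete-case rule could add a second selection in the same direction, in a study that aims at the whole spectrum of patients with FM-UE ≤ 50 and at generalizable conclusions.

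**Working it through.** **The plan's own figure.** The only patient number available is the expected enrolment: "we will probably only reach 200 patients" (Recruitment). It has no formula behind it. The recruitment arithmetic in that section is 2000 × 1.5 × 0.7 = 2100 (stated as about 2000), × 0.4 = 840 (stated as 800), × 0.5 = 420 (stated as approximately 400). All of these losses come before inclusion, so none of them says how many enrolled patients will have complete records.

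**Items that a strict reading requires**

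- Acute phase, Table 2: NIHSS, blood sample, mRS, MRI or CT, SAFE, grip strength, FMA, ARAT, BI, Bells test, AST, BDI, SS-QOL, EEG, MEP = 15.
- Rehabilitation, Table 3: admission, 14-day interval and discharge, counted as 3.
- Day-90 visit, counted as 1.
- Total k = 15 + 3 + 1 = 19. DILA-S, described in the text but absent from Table 2, is not counted.

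**Complete-case yield.** Let c be the completeness of each item. The article gives no value, so c is an assumption.

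- Independent gaps: remaining = 200 × c^19.
- Fully overlapping gaps (the same patients miss everything): remaining = 200 × c.

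| c (assumed) | c^19 | Remaining, independent | Lost, independent | Lost, full overlap |
|---|---|---|---|---|
| 99% | 0.826 | 165 | 35 | 2 |
| 98% | 0.681 | 136 | 64 | 4 |
| 97% | 0.561 | 112 | 88 | 6 |
| 95% | 0.377 | 75 | 125 | 10 |

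The dependence between gaps matters at least as much as the rate. At 95% completeness the loss lies anywhere from 10 to 125 of 200.

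**Outcome-only reading.** If only the day-90 status must be known and predictors are imputed, the loss is the day-90 loss alone. At an assumed 0%, 5%, 10% or 20%, that leaves 200, 190, 180 or 160.

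**Severity, for illustration only.** Assume that half of 200 patients are severely affected.

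- Completeness 80% in severe and 95% in other patients: 80 + 95 = 175 remain, and the severe share is 80/175 = 46% instead of 50%.
- Completeness 60% and 85%: 60 + 85 = 145 remain, and the severe share is 60/145 = 41%.

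**The case against.** The best defence is that a complete data set means only closed follow-up. A patient who dies counts as complete, yet has no day-90 FM-UE and, after an early death, perhaps no rehabilitation record. So the term cannot mean that every field is filled for everyone, and the outcome-only reading would fit the imputation paragraph. This stands as a possible reading. It is not what the sentence says, though: the word *including* makes day 90 one part of a larger complete set, and nothing in the article limits completeness to the outcome.

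A reader might infer several stronger points that the article does not support.

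- **That a large share of patients will be discarded.** No missing-data rate is given. Independence across items is pessimistic, and five of the 15 Table 2 items (NIHSS, mRS, BI, blood sample, imaging) are routine work-up. The article also describes missing-entry warnings, home visits for day 90 and an expectation that patients will not discontinue. These safeguards limit withdrawal and forgotten entries, but they do not recover a test that the patient could not do.
- **That the protocol itself expects missingness to follow severity.** The Discussion speaks of who is recruited, not of missing data. It argues that the extra tests need little active participation and that enough severe cases will be captured. Selective missingness is an inference from fitness-dependent testing and proxy consent.
- **That the most severe cases are removed.** Deaths are expressly kept.
- **That patients without rehabilitation records are lost in number.** Those refusing rehabilitation are excluded, and the Recruitment section counts out those too frail for it or whose deficit resolves before inclusion. How many others lack records is unknown.
- **That the loss of precision can be put as a confidence interval for R².** That needs an ordinary regression with an assumed number of predictors, which is not the planned nested cross-validated lasso and Gaussian-process model.

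It is also fair to say that imputation details are often left to a fuller plan. Here, however, both rules are stated and they disagree.

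**Conclusion.** The conflict is real and rests on the text alone. The analysis-set sentence, taken literally, gives a complete-case analysis and leaves the announced imputation without a role.

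The size of the consequence cannot be derived from the article. With 19 items at an assumed 95% to 99% completeness, the loss is 35 to 125 of 200 under independence and 2 to 10 under full overlap. Under-representation of severely affected patients is plausible, and it would add to the recruitment bias that the Discussion concedes, but it is not demonstrated.

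Whether at least 200 patients will be recruited, or probably only 200, is a separate and minor wording matter.

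**What to change.** Replace the analysis-set sentence in Statistical methods with a rule along these lines: all participants with an initial FM-UE and a known day-90 status (examination or death) are analysed; a complete set of predictors is not required.

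Then:

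1. Impute missing predictors, but not the day-90 outcome, within the training folds of the nested cross-validation.
2. Keep the complete-case analysis as a sensitivity analysis.
3. Compare included with excluded patients on baseline severity.
4. State separately how participants who die enter the FM-UE endpoint. The current rule admits them, but the endpoint formula gives them no value.

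The cost is a change of wording and a little more analysis work. The imputation methods are already named in the article, and no additional data are needed.
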